### Clinical practice guidelines for the use of antenatal magnesium sulphate for neuroprotection of the fetus, infant and child

Researchers at the Australian Research Centre for Health of Women and Babies (ARCH) within the Robinson Institute at the University of Adelaide, led a rigorous guideline development process, culminating in the 2010 National Health and Medical Research Council (NHMRC) endorsed Australian and New Zealand clinical practice guidelines for magnesium sulphate for women at risk of early preterm (less than 30 weeks gestation), imminent birth (planned or definitely expected within 24 hours) [10]. These clinical practice guidelines *‘Antenatal magnesium sulphate prior to preterm birth for neuroprotection of the fetus, infant and child’*[10] provide detailed guidance in the form of nine evidence-based recommendations and six good practice points on how and when to use antenatal magnesium sulphate prior to very preterm birth for fetal neuroprotection (Table 1).

**Table 1 T1:** **Summary of clinical recommendations from the NHMRC endorsed Australian and New Zealand clinical practice guidelines **[10]

**Clinical recommendations**	**Grade^**	**Chapter**
**In women at risk of early preterm imminent birth, use magnesium sulphate for neuroprotection of the fetus, infant and child:**	A	4-7
• When gestational age is less than 30 weeks.	B	8
• When early preterm birth is planned or definitely expected within 24 hours (when birth is planned, commence magnesium sulphate as close to four hours before birth as possible).	A	9
• Intravenously with a 4 gram loading dose (slowly over 20–30 minutes) and 1 gram per hour maintenance dose via intravenous route, with no immediate repeat doses. Continue regimen until birth or for 24 hours, whichever comes first.	C	10
• Regardless of plurality (number of babies in utero).	B	11
• Regardless of the reason women (at less than 30 weeks gestation) are considered to be at risk of preterm birth.	B	12
• Regardless of parity (number of previous births for the woman).	B	13
• Regardless of anticipated mode of birth.	B	14
• Regardless of whether or not antenatal corticosteroids have been given.	B	15

^These grades are based on the NHMRC’s standards for grading recommendations for developers of guidelines, and reflect the degree of trust that can be placed in a particular recommendation based on the strength of the evidence (with A indicating the highest degree of trust).

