#### *For hospital sites participating in the ‘WISH audit of uptake and health outcomes data collection’*

All eligible women who give birth after 22 completed weeks gestation and before 30 weeks gestation (excluding known lethal congenital anomalies) at the participating hospitals will be given the project information sheet and counselled by a member of the research team about participating in the project. Women will then be given the opportunity to discuss their participation with their families. Informed, written consent will be obtained by the research team if the woman agrees to participate in the project.

For the woman and her baby, consent to enrol in the project will provide consent to access information from the maternal and neonatal clinical records. Mothers of children who survive to primary hospital discharge will be invited to complete the Ages and Stages Questionnaire at 12 and 24 months corrected age, providing information about their child’s health and development [23].

Information will be collected from the maternal case record on maternal demographic characteristics, mode of birth, reason for preterm birth, use of antenatal corticosteroids, tocolysis, eligibility for magnesium sulphate, and whether magnesium sulphate was given. If magnesium sulphate was given, the reason for magnesium sulphate, total dose administered, gestational age given, whether loading, maintenance or repeat doses were used, and timing prior to birth will be recorded together with any adverse effects. For the infant, stillbirth and death of live-born infants prior to primary hospital discharge will be collected.

Information on early child health will also be sought from the child health record up to two years corrected age, in liaison with the family, from any formal paediatric assessment of motor function and psychological assessment.

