#### For hospital sites participating in the ‘WISH audit of uptake and health outcomes data collection’

Project outcomes for the early phase of the project (Year 1) will be compared with the later intervention phase (Years 2 and 3). The proportion of eligible women prescribed magnesium sulphate will be analysed with Chi^2^ tests (p values of 0.05 regarded as statistically significant) for the earlier period, compared with the later period. Similarly, the rates of death prior to primary hospital discharge for the earlier project period will be compared with the later period. Individual adverse events will be presented as average rates per woman receiving magnesium sulphate. Uptake of magnesium sulphate and rates of death prior to primary hospital discharge after birth will be graphed over time to assess trends; the proportion of infants born during Year 1 with cerebral palsy (identified by age two) will be compared with proportions identified in the literature; with the opportunity, subject to further funding, to compare with proportions born during Years 2 and 3.

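### Uptake is tested by an unadjusted before-after Chi-squared comparison, so a change in the mix of eligible women can add to or hide a change in practice, and a pooled rise need not extend to every group the guideline covers.

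*Protocol article*

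**What the plan says.** Uptake is the first primary health outcome listed for the audit hospitals. It is defined as a proportion among women judged eligible under the bi-national guideline, followed over three consecutive years.

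The Data analyses section for these hospitals sets the contrast: "Project outcomes for the early phase of the project (Year 1) will be compared with the later intervention phase (Years 2 and 3"). It then names the test. "The proportion of eligible women prescribed magnesium sulphate will be analysed with" Chi-squared tests, with "p values of 0.05 regarded as statistically significant". The only other uptake analysis is that results "will be graphed over time to assess trends". Neither analysis mentions adjustment, stratification or breakdown by patient factor.

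The background section says the guideline contains "nine evidence-based recommendations and six good practice points". Table 1 lists the nine recommendations. Five extend treatment across a patient factor, for example "Regardless of plurality (number of babies in utero") and "Regardless of the reason women (at less than 30 weeks gestation) are considered to be at risk of preterm birth". The other three concern parity, anticipated mode of birth and antenatal corticosteroids.

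Under Data collection and management, the items taken from the maternal record include "mode of birth, reason for preterm birth, use of antenatal corticosteroids, tocolysis, eligibility for magnesium sulphate, and whether magnesium sulphate was given". Plurality and parity are not named there.

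**The concern.** Year 1 and Years 2 and 3 are compared without randomisation. If the chance of treatment differs between groups of eligible women, such as planned births and spontaneous labour, the pooled proportion depends on practice within each group and on the share of each group. A crude test cannot separate the two. A shift towards more readily treated women would look like better implementation, and a shift the other way would hide it.

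Separately, a pooled rise can come from some groups while others barely change. The project exists to put this guideline into practice, and it also aims to give hospitals indicators for quality improvement. More than half of the recommendations concern breadth of use across patient groups, so where uptake rose is of direct interest. The article collects reason for preterm birth, mode of birth and corticosteroid use but gives them no role in the stated uptake analysis.

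**Working it through.** **Plan's own figure.** There is none to reproduce. The article states no number of women, baseline or target uptake, or power. All rates, shares and sample sizes below are assumptions. Later-period numbers are taken as twice Year 1, which supposes stable births per year, and alpha as two-sided 0.05.

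**Step 1, the count.** Table 1 has nine graded rows. Five are of the regardless-of form: plurality, reason, parity, anticipated mode of birth, corticosteroids.

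**Step 2, the data.** Reason for preterm birth, mode of birth and corticosteroid use are named as collected. Gestational age at birth must be known because it defines the cohort. Plurality and parity are not named.

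**Step 3, change in mix with no change in practice.** Let uptake be a in one group and b in the other, constant over time, and let the share of the first group go from m1 to m2. Pooled uptake is p = m·a + (1 − m)·b, so the shift is (m2 − m1)(a − b).

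- Smallest case: 0.05 × 0.20 = 0.01, or 1 point.
- Largest case: 0.20 × 0.40 = 0.08, or 8 points.

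Chance of p < 0.05 with practice unchanged:

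| a, b | share m1 to m2 | pooled uptake | 250 in Year 1 | 500 | 1000 |
|---|---|---|---|---|---|
| 80%, 60% | 50% to 55% | 70% to 71% | 6% | 7% | 9% |
| 80%, 50% | 50% to 60% | 65% to 68% | 13% | 22% | 38% |
| 80%, 40% | 40% to 60% | 56% to 64% | 56% | 85% | 99% |

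One case in full, with uptake of 85% and 45% and the share of the first group going from 30% to 40%:

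- Early: 0.30 × 0.85 + 0.70 × 0.45 = 0.57. Later: 0.40 × 0.85 + 0.60 × 0.45 = 0.61.
- With 1000 and 2000 women the overall proportion is (570 + 1220)/3000 = 0.597.
- Null standard error = √(0.597 × 0.403 × (1/1000 + 1/2000)) = 0.0190, so z = 0.04/0.0190 = 2.105 and p = 0.035.
- Standard error under the alternative = √(0.57 × 0.43/1000 + 0.61 × 0.39/2000) = 0.0191. The chance of significance is Φ((0.04 − 1.96 × 0.0190)/0.0191) ≈ Φ(0.145), about 56%. With 250 and 500 women it is about 18%.
- If the share goes only from 30% to 35%, pooled uptake goes from 57% to 59%. The chances are then about 18% (1000 in Year 1) and 8% (250).

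**Step 4, a group left behind.** Suppose uptake starts at 30% in all women and rises to 80%, except in a group with share s that stays at 30%. Later pooled uptake is s × 0.30 + (1 − s) × 0.80.

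- s = 15%: 0.045 + 0.680 = 72.5%, a rise of 42.5 points.
- s = 30%: 0.090 + 0.560 = 65%, a rise of 35 points.
- s = 50%: 0.150 + 0.400 = 55%, a rise of 25 points.

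With 100 women in Year 1 and 200 later, the Chi-squared test has 99% to 100% power in all three cases. A significant pooled result therefore says little about whether each group was reached. This does not depend on any change in mix, and a larger overall rise does not cure it.

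**The case against.** The strongest reply is that this is a condensed article. Covariate lists, sensitivity analyses and subgroup tables usually sit in a fuller plan, and naming one test does not exclude others. That stands for the descriptive tables, which alone would only be extra reporting. It does not dispose of the main point: the article goes as far as naming a test and a significance threshold for a primary outcome, and that test is crude in a non-randomised contrast.

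A second reply is that the test answers its own question. The outcome is overall uptake among eligible women, untreated groups stay in the denominator and pull it down, and nowhere does the article promise to show adoption of each recommendation separately. This also stands. There is no contradiction with the stated aims, only a limit on what a significant result means.

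A reader might infer that the audit cannot show whether the regardless-of recommendations were adopted. The documents do not support that, because three of the five factors are collected for each woman and uptake can be broken down by them. A reader might also infer that case mix is ignored altogether. It is not: the measure is confined to guideline-eligible women, which may remove some births too unexpected to treat. But the guideline makes women eligible across all five factors, so variation between those groups remains in the denominator.

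Finally, adjusting for everything collected could do harm. Corticosteroid use is a concurrent care decision that may change with the education and local-protocol work. Recorded mode of birth may differ from the anticipated mode in Table 1. Conditioning on either could remove part of the change being measured. This stands and shapes the fix.

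**Conclusion.** The point holds as a limitation of the stated uptake analysis that can be remedied. The unadjusted period comparison can be moved by a change in the mix of eligible women, and a pooled rise does not establish that uptake improved across the groups Table 1 names.

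The size rests entirely on assumed inputs. A 5 to 20 point shift in mix with a 20 to 40 point gap in uptake gives 1 to 8 points, and a chance of a significant result without any change in practice from about 6% (1-point shift, 250 women in Year 1) to about 99% (8-point shift, 1000 women). Both the mix and the group-specific uptake must differ for this to happen. Nothing in the article shows that mix drift is likely to decide the result. Beside the 25 to 42.5 point rises in Step 4 it would be secondary, and the project is aiming for a large rise in a therapy that was not previously routine. The group-left-behind problem remains even then.

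**What to change.** In the Data analyses section for the audit hospitals:

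1. Keep the Chi-squared test. Beside it, add the Year 1 versus Years 2 and 3 difference in uptake with a 95% confidence interval, adjusted for, or standardised to a common distribution of, reason for preterm birth and gestational age. Include plurality and parity if the data form records them, and check whether it does.
2. Leave corticosteroid use and actual mode of birth out of this main adjustment, for the reasons given above.
3. Report uptake by period, with confidence intervals, by reason for preterm birth, mode of birth and corticosteroid use. Present these as descriptive, without significance claims within groups.

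The cost is some analysis wording and a few tables, largely from data already collected. Plurality and parity may need to be confirmed or added as items. Some strata will be small and their estimates imprecise, which the intervals will show.

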### Entry criteria

#### *Hospital sites eligible to receive active implementation interventions*

All 25 tertiary level maternity hospitals within Australia and New Zealand with a neonatal intensive care unit will be eligible to receive active implementation interventions (Additional file 1). Clinical practice recommendations are that women at risk of an early birth are transferred to an institution with neonatal intensive care facilities. The tertiary level facilities are therefore the most likely sites where magnesium sulphate for neuroprotection will be administered immediately prior to imminent preterm birth, as per the bi-national clinical practice guideline recommendations [10].

All eligible hospitals will be invited to join the project and to nominate a local clinical implementation leader to be a member of the ‘WISH Study Group’ with the aim, at their institution, of promoting the use of antenatal magnesium sulphate as a fetal neuroprotective therapy, prior to imminent, early preterm birth; with the option of participating in the ‘WISH audit of uptake and health outcomes data collection’, monitoring uptake, mortality and cerebral palsy.

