### Implementation interventions

#### *Active dissemination and strategies to implement the Australian and New Zealand antenatal magnesium sulphate clinical practice guidelines at all eligible hospital sites*

A package of active implementation strategies (chosen on the basis of likely benefit) will include the guided introduction and local adaptation of guideline recommendations, in-service education [14,17], academic detailing [18], reminders [14] and audit and feedback [13,14,16]. The local clinicians will be encouraged to adapt the antenatal magnesium sulphate guidelines in line with their local hospital protocols and produce algorithms to communicate work flow and decision points [13].

Each hospital will also be provided with a WISH Project Guideline Action Pack (GAP). The GAP includes a ‘tool kit’ of information developed by the WISH Study Group to aid in implementation [14,20], including the NHMRC endorsed guidelines, educational materials including a PowerPoint for use in in-services, health professional and consumer information (Additional files 2 and 3), posters (Additional file 4) and reminder hospital record inserts (Additional file 5).

Each hospital will be strongly encouraged to form a local implementation group (or identify a local leader) [13,19], with the actual composition to be determined at the local level. The local implementation group will be guided to use the GAP materials to suit local needs. Formal and informal in-service education sessions will be encouraged [17], as well as one-on-one discussions with health professionals caring for women at risk of very preterm birth to address any individual questions and concerns (academic detailing) [18].

We will use audit and feedback, as this has been identified as an effective strategy [13], particularly where baseline adherence to recommended practice is low and where intensive feedback can be given [16]. A regular newsletter will be sent to all hospitals for distribution to relevant local health professionals highlighting overall progress in the project, and giving information on the latest rates of uptake of magnesium sulphate for neuroprotection from those sites participating in the ‘WISH audit of uptake and health outcomes data collection’.

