#### *Primary health outcomes for hospital sites participating in the ‘WISH audit of uptake and health outcomes data collection’*

• The proportion of women giving birth after 22 completed weeks gestation and before 30 weeks gestation (excluding known lethal congenital anomalies) receiving antenatal magnesium sulphate (judged to be eligible for such treatment according to the bi-national clinical practice guidelines [10]) during three consecutive years;

• Deaths prior to primary hospital discharge of babies born after 22 completed weeks gestation and before 30 weeks gestation during three consecutive years;

• Cerebral palsy rate at early childhood follow-up (two years corrected age) in babies born alive after 22 completed weeks gestation and before 30 weeks gestation in the first year of three consecutive years. The importance of follow-up of this cohort is recognised; further support will be sought to ensure the timely and ongoing collection of the highest quality follow-up data including at preschool and early school age.

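### The Chi-squared test named for the primary uptake outcome makes no allowance for hospital, so its p-value will be too small if change over time differs between hospitals

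*Protocol article*

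**What the plan says.** Uptake is the first-listed primary health outcome for the audit hospitals, measured "during three consecutive years" (Project outcomes, primary health outcomes). For these hospitals the Data analyses section states: "Project outcomes for the early phase of the project (Year 1) will be compared with the later intervention phase (Years 2 and 3"). It then fixes the method for uptake, which "will be analysed with Chi^2^ tests (p values of 0.05 regarded as statistically significant) for the earlier period, compared with the later period". The only other stated analysis of uptake is a graph over time. Deaths before primary discharge are to be compared between the same periods, apparently by the same approach.

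Three features of the design bear on this test:
- The intervention acts on hospitals. Under Implementation interventions: "The local clinicians will be encouraged to adapt the antenatal magnesium sulphate guidelines in line with their local hospital protocols".
- Audit participation is a choice for each hospital. Under Entry criteria, hospitals are invited to join "with the option of participating in the" audit. The text shown does not give the number of audit hospitals; it gives only the number eligible, 25.
- Women enter one by one. Under Data collection and management: "Informed, written consent will be obtained by the research team if the woman agrees to participate in the project".

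**The concern.** A plain Chi-squared test treats the Year 1 women and the Years 2 and 3 women as two sets of independent observations. Here women are grouped in hospitals, and women in one hospital share its local protocol and its pace of adoption. The article itself expects local factors to matter: it describes organisational barriers in the Background and offers sites an assessment of local barriers and enablers.

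The component that harms the test is variation between hospitals in the change over time. The test's standard error leaves this out, so the p-value is too small when the result is generalised beyond the hospitals observed. Stable differences in level between hospitals do not cause this.

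A second, separate risk concerns the estimate. If hospitals with low and high uptake supply different shares of the women in the two periods, an unstratified comparison mixes that shift with the real change.

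Uptake is the outcome most directly tied to the package, and the Abstract says that the project will give insight into how effective the strategy is. An overstated level of certainty would carry straight into that conclusion.

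**Working it through.** The article gives no sample size, power, uptake rate, effect size or intracluster correlation, so there is no figure to reproduce. The calculations below show sensitivity under assumptions.

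**Inputs from the article:** Chi-squared test, alpha 0.05, one year against two years, at most 25 hospitals.

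**Assumed inputs:** 5 to 25 audit hospitals; 40 or 80 women per hospital in Year 1 and twice that number later; uptake centred on 50%; between-hospital SD 0.8 (logit); hospital-by-period SD *s* from 0 to 0.6 (logit), drawn independently in each period; no average change.

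**Step 1. What *s* means.** The SD of a hospital's change is *s*√2 on the logit scale. Near 50% uptake, one logit unit is worth about 0.25 in proportion. So *s* = 0.2, 0.4 and 0.6 give 0.2 × 1.414 × 0.25 = 0.07, then 0.14 and 0.21. Hospitals' true changes would vary with an SD of about 7, 14 or 21 percentage points.

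**Step 2. Simulated false-positive rate** (20,000 replicates per scenario, nominal 5%):

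| Hospital-by-period SD | Chi-squared, 40 per hospital in Year 1 | Chi-squared, 80 per hospital in Year 1 |
|---|---|---|
| 0 (stable level differences only) | 3.8–3.9% | 3.6–3.8% |
| 0.2 | 8.7–9.2% | 13.4–13.7% |
| 0.4 | 21–22% | 33–34% |
| 0.6 | 34–35% | 48% |

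With no hospital effects at all, the Chi-squared test gave 4.9% to 5.4%, as it should. The number of hospitals hardly mattered. A paired t test on one before-after difference per hospital stayed between 4.6% and 5.1% throughout.

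A second set of assumptions (8 to 20 hospitals, 60 women per hospital-year, between-hospital SD 0.5) agrees. SDs of 0.2, 0.3 and 0.5 gave about 12–13%, 21–23% and 37–38%. With no hospital-by-period variation and balanced contributions, the rate was 4.0–4.6%.

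**Step 3. Analytic check.** Let ρ be the within-period and π the between-period intracluster correlation, with *m* women per hospital early and 2*m* later.

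Design effect = {[1+(m−1)ρ]/m + [1+(2m−1)ρ]/(2m) − 2π} / {1/m + 1/(2m)}; actual alpha = 2[1 − Φ(1.96/√design effect)].

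With m = 40 and ρ = 0.05, the first two terms are 2.95/40 + 4.95/80 = 0.0738 + 0.0619 = 0.1356, and the denominator is 0.0375.
- π = 0.05: (0.1356 − 0.10)/0.0375 = 0.95, alpha 4.4%.
- π = 0.04: (0.1356 − 0.08)/0.0375 = 1.48, alpha 10.8%.
- π = 0.025: (0.1356 − 0.05)/0.0375 = 2.28, alpha 19.5%.

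A small gap between the two correlations is enough to double the error rate.

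**Step 4. Shift in shares (hypothetical).** Take two groups of hospitals with constant uptake of 40% and 70%.
- Low-uptake share falls from 50% to 40%: 0.5×0.4 + 0.5×0.7 = 0.55 against 0.4×0.4 + 0.6×0.7 = 0.58. This is a spurious +3 points, significant in about 17% of studies with 400 against 800 women and 29% with 800 against 1,600.
- Low-uptake share falls from 50% to 30%: 0.55 against 0.61, a spurious +6 points, significant in about 51% and 80%.
- No shift: the spurious difference is 0.

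**The case against.** A reader might infer that ignoring hospital makes the p-value invalid outright. It does not. In a before-after comparison within the same hospitals, stable differences largely cancel, and the test is then slightly conservative. The inflation needs hospital-by-period variation, for which the article gives no value. This stands, and the point is conditional for that reason.

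A reader might also infer that the result is confounded by which hospitals contribute in each period. The article does not support that. Uptake is defined over one three-year window, and Ethical considerations reports approval as already granted at each participating site, which suggests a set of sites already named. Optional participation and individual consent make a drift in shares possible, no more. Late joiners could in principle even reverse the sign: if 12 equal-sized hospitals rise from 60% to 65% and 4 join late at 30%, pooled uptake is (12×0.65 + 4×0.30)/16 = 56%. That case is invented.

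The strongest objection concerns the target of inference. The simulated null lets each hospital's true rate move, so the audited hospitals' average really does change in each replicate. Rejection is false only when generalising beyond them. The eligible set is finite, and the Aims include monitoring and quality improvement within participating hospitals. For the narrow question of what happened there, most of the inflation disappears. This limits the claim without removing it, because the Abstract seeks insight into the strategy's effectiveness. Even the narrow question is better served by a hospital-stratified comparison.

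Finally, the article does not say pooled, and it condenses a fuller plan. But it names the test for a primary outcome, and an unstratified comparison is the natural reading. It is also true that, without a concurrent control, no p-value can attribute the change to the package. That is no reason to misstate the precision of the change itself.

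**Conclusion.** The concern holds in conditional form. The named test does not fit an intervention delivered and adapted hospital by hospital. If change over time differs between hospitals, the p-value will be too small for conclusions beyond the audited hospitals: roughly 9% to 48% false positives for the assumed SDs of 0.2 to 0.6 and 40 to 80 women per hospital in Year 1. If hospitals differ only in level and contribute constant shares, the rate is about 4% and no correction is needed for validity. Bias from shifting shares is possible but not shown. Hospital count, women per hospital, uptake level and variance components are all assumptions. A very large rise in uptake would probably be significant under either method, but its uncertainty would still be understated.

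**What to change.** Replace the unstratified Chi-squared test with a comparison within hospital, by one of two routes:
- a paired hospital-level analysis of before-after differences, preferable if few hospitals take part; or
- a logistic mixed model with period as a fixed effect, hospital and hospital-by-period effects, and a small-sample correction.

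Report the within-hospital difference or risk ratio with a 95% confidence interval. Add a sensitivity analysis restricted to hospitals contributing in all three years, which also addresses any change in the set of sites. State whether conclusions are meant for the audited hospitals only or for the package more widely.

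The change is to analysis wording. Data come from case records at the participating hospitals, so hospital should be known for every woman and no new data are needed. The price is a wider confidence interval and a little more analysis work. An unweighted paired analysis also describes the average hospital rather than the average woman, which should be stated.

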### Magnesium sulphate and prevention of cerebral palsy: the evidence base

Nearly twenty years ago, a case–control study first described the association between antenatal magnesium prior to preterm birth and the prevention of cerebral palsy [8]. The updated Cochrane review ‘Magnesium sulphate for women at risk of preterm birth for neuroprotection of the fetus’ [9], including five randomised controlled trials, showed for the first time that magnesium sulphate given to women prior to preterm birth can reduce the risk of death or cerebral palsy (risk ratio 0.85, 95% confidence interval 0.74 to 0.98; 4446 infants), and of cerebral palsy alone (risk ratio 0.68, 95% confidence interval 0.54 to 0.87; 6145 infants). The Cochrane review showed that 63 women need to be treated with antenatal magnesium sulphate for neuroprotection for one baby to avoid cerebral palsy. The corresponding number needed to treat to benefit for combined death or cerebral palsy was 42 [9]. This was a very important finding, as few interventions to date have been found to prevent the devastating and lifelong consequences of cerebral palsy.

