## Methods/Design

A prospective cohort study will be conducted. The project will also have a qualitative component which will assess barriers and enablers to changes in practice.

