#### *Women eligible at hospital sites participating in the ‘WISH audit of uptake and health outcomes data collection’*

Eligible women at hospitals participating in the ‘WISH audit of uptake and health outcomes data collection’ (Additional file 1) will be those giving birth after 22 completed weeks of gestation and before 30 weeks gestation (excluding women carrying fetuses with known lethal congenital anomalies).

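### In-hospital death, a primary outcome, is compared between periods without adjustment for gestational age or for siblings, and a modest case-mix shift could equal the implied effect

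*Protocol article*

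**What the plan says.** The article describes the design in one line: "A prospective cohort study will be conducted". In the data analyses section for audit hospitals it sets the contrast: "Project outcomes for the early phase of the project (Year 1) will be compared with the later intervention phase (Years 2 and 3"). Uptake is to be analysed with Chi-squared tests, with "p values of 0.05 regarded as statistically significant". The next sentence carries the approach over to mortality: "Similarly, the rates of death prior to primary hospital discharge for the earlier project period will be compared with the later period". Death rates are also to be graphed over time. No covariate, stratification, standardisation or allowance for siblings is mentioned anywhere in the article.

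Mortality is listed among the primary health outcomes: "Deaths prior to primary hospital discharge of babies born after 22 completed weeks gestation and before 30 weeks gestation during three consecutive years". The eligible women are "those giving birth after 22 completed weeks of gestation and before 30 weeks gestation", so one rate pools the whole range. Multiple pregnancies are not excluded, and the guideline summary (Table 1) recommends treatment whatever the number of fetuses.

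On what is recorded, the data collection section says: "For the infant, stillbirth and death of live-born infants prior to primary hospital discharge will be collected". The items it lists include neither plurality nor gestational age at birth, although eligibility requires the latter.

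On the size of the treatment effect, the evidence section gives a number needed to treat of 63 for cerebral palsy and adds: "The corresponding number needed to treat to benefit for combined death or cerebral palsy was 42". It gives no figure for death alone.

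**The concern.** The two periods are not randomised and there is no concurrent control. The crude death rate therefore depends on which babies are born in each period as well as on how their mothers are treated. Gestational age is the obvious case-mix variable, and it must be known for every case because it determines eligibility, yet the stated comparison does not use it.

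The audit has features through which the mix could change systematically. Hospitals choose whether to take part, and each woman gives written consent after an eligible birth. If the mix did shift, a difference in deaths in either direction could be read as an effect of the implementation programme on a primary outcome.

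Two smaller points belong with this. Babies of one mother are not independent, which a plain Chi-squared test ignores. The article also leaves some doubt about stillbirths: the death outcome refers to babies born, the cerebral palsy outcome to babies born alive, and both stillbirth and death of live-born infants are collected.

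**Working it through.** The article states no sample size, power, baseline mortality or expected effect on death, so there is no design figure to reproduce. The checks below ask how large a death effect its own evidence implies, and what could match it.

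**1. Implied effect on death.** Inputs from the evidence section: number needed to treat 42 for death or cerebral palsy (risk ratio 0.85, 4446 infants) and 63 for cerebral palsy (risk ratio 0.68, 6145 infants).

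- Risk differences: 1/42 = 2.38 points and 1/63 = 1.59 points.
- Death by subtraction: 2.38 − 1.59 = 0.79 points, if uptake went from none to all.
- Diluted by the change in uptake: 0.40 × 0.79 = 0.32 points and 0.55 × 0.79 = 0.44 points. The article states no uptake target. The 40-point rise is an assumption, and the 55-point rise borrows the article's corticosteroid example (20% to 75%).

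The subtraction is approximate because the two figures rest on different infant totals.

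**2. Implied baseline.** Control risk = 1 / (NNT × (1 − RR)).

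- Death or cerebral palsy: 1 / (42 × 0.15) = 15.9%.
- Cerebral palsy: 1 / (63 × 0.32) = 5.0%.
- Death by subtraction: about 10.9%. An assumed 15% is used as an alternative below.

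**3. Case mix needed to match the effect.** Break-even shift in share = effect / mortality gap between the lowest and highest gestational-age strata. The article gives no mortality by gestation, so the gap is assumed.

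| Assumed gap | Shift matching 0.44 points | Shift matching 0.79 points |
|---|---|---|
| 10 points | 4.4 points | 7.9 points |
| 20 points | 2.2 points | 4.0 points |
| 50 points | 0.9 points | 1.6 points |

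**4. Power of the crude test.** Assumptions: two-sided 0.05, equal births per year (so 1:2), and 500 to 2000 Year 1 babies. For example, with 1000 Year 1 babies, 10.9% mortality and an effect of 0.44 points:

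- SE = √(0.109 × 0.891/1000 + 0.1046 × 0.8954/2000) = 1.20 points.
- z = 0.437/1.20 = 0.364.
- Power = Φ(0.364 − 1.96) + Φ(−0.364 − 1.96) = 0.055 + 0.010 = 6.5%.

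| Effect | Power at 10.9% mortality, 500 to 2000 babies | Power at 15% mortality, 500 to 2000 babies |
|---|---|---|
| 0.32 points | 5% to 7% | 5% to 6% |
| 0.44 points | 6% to 8% | 6% to 7% |
| 0.79 points | 8% to 16% | 7% to 13% |

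At 10.9% mortality, 80% power for 0.44 points would need about 58,810 Year 1 babies. At 15% it would need about 77,707.

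**5. Multiples.** With a share s of babies in twin pairs and within-pair correlation ρ, the variance is inflated by 1 + sρ. Assuming s = 25% to 35% and ρ = 0.3 to 0.5, this is 1 + 0.25 × 0.3 = 1.08 to 1 + 0.35 × 0.5 = 1.18. This is a modest understatement, and all of its inputs are assumed.

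**The case against.** The strongest reply is that the article is a condensed account. It names the Chi-squared test for uptake only, the death sentence is tied to it loosely, and covariates or clustering may be set out in a plan not shown here. That lowers confidence. It does not remove the point, because the article does state a method for a primary outcome, and followed as it stands that method is crude.

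A reader might infer that case-mix shifts will swamp the effect, or that a p-value below 0.05 would most likely reflect case mix. The documents support neither. They give no mortality gradient and no evidence that the mix will change. With a 10-point gap, a shift of 4.4 points would be needed to match 0.44. Chance variation in case mix is already inside the binomial variance, so only a systematic shift biases the comparison. A significant result could also simply be chance.

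It would also be too firm to say that the article leaves almost no effect on death. Applying the quoted confidence intervals to the implied control risks gives 0.3 to 4.1 points for death or cerebral palsy and 0.6 to 2.3 points for cerebral palsy, so their difference is very uncertain.

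Two further replies are fair. Adjustment would remove neither secular change in neonatal care nor low power. And the article already speaks of monitoring deaths, though it still ranks them as a primary outcome. On stillbirths, the data collection wording and the mention of death after birth in the plan for the graph both favour a live-birth outcome, so that ambiguity is minor.

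**Conclusion.** The point holds in a limited form. As written, the comparison of a primary outcome is an unadjusted, non-randomised before-after contrast that pools all eligible gestations and treats siblings as independent. The implied death effect is at most about 0.8 points, and about 0.3 to 0.4 points for an assumed 40 to 55 point rise in uptake. A systematic shift of about 1 to 2 points between the extreme gestational-age strata could equal or exceed the 0.44-point figure if their mortality differs by 20 to 50 points. Whether such a shift will occur cannot be judged from the article.

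The low-power conclusion is sturdier. It holds at both baseline rates tried and across the assumed range of births. A non-significant result would say little, and a significant one would not by itself show that the implementation worked.

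**What to change.** - Replace the crude comparison of deaths with logistic regression on period, adjusted for gestational age at birth in completed weeks, hospital and, once it is confirmed as recorded, plurality. Cluster the standard errors on mother.
- Report the adjusted risk difference with its 95% confidence interval as a monitoring result. Say explicitly that it is not evidence that the implementation worked, because secular change and low power remain.
- State whether the outcome is death of live-born infants before primary discharge, and report stillbirths separately, since both are already collected.

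The cost is slightly more analysis work and a check that plurality is on the data form. Gestational age is already needed to establish eligibility.
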